### Ecological Momentary Assessment

We developed a study-specific smartphone application using the LifeData platform. The app is free to use and compatible with both iOS and Android devices. Participants are asked to download the app during the baseline laboratory session, with guidance from an experimenter. They are also given a user instruction and FAQ document to take home and refer to as needed; study contact information is included for assistance.

Participants use their own smartphones to complete the EMA unless they either do not own one or own a device with a different operating system. Those without an appropriate smartphone borrow a study iPod Touch device for this activity. The app interface across these systems is comparable.

EMA is to commence following the laboratory-based visit. Participants receive a push notification to complete EMA twice daily over the course of 14 days: once at 12:00 p.m. and once at 8:00 pm, both times within a 2-h active window. Push notifications begin immediately after app download, so depending upon the time of day of the baseline assessment, participants begin receiving notifications either that afternoon or that evening. This timing, frequency, and duration was based on pilot work conducted with a non-medical sample (Langer et al., 2020). If participants do not begin to complete the assessment within the 2-h response window, the notification expires. Reminder notifications are included for each assessment; these arrive every 20 min, up to 5 times, until a participant responds or the notification expires.

At each EMA, patients and partners are asked to answer a series of questions. Branching logic minimizes participant burden. First, participants are asked if they talked to their partner during a given time frame (since awakening for the 12:00 p.m. time point or since the last assessment for the 8:00 p.m. time point). If no, a single item designed to assess reasons for not talking is posed (I didn’t have any contact with my partner; I had nothing to talk about; I didn’t feel well; I didn’t want to bring up topics that could be upsetting; other). If yes, questions designed to assess perceptions of the conversation follow. These are listed in Table 2.

**TABLE 2 T2:** Smartphone-delivered ecological momentary assessment (EMA) items.

Item	Construct
To what extent was this conversation related to your/your partner’s cancer?	Cancer relatedness
How important was this conversation to you?	Importance
**Predictors**	
To what extent did you express your feelings?	Enacted disclosure
To what extend did you hold back from expressing your feelings?	Enacted holding back
To what extent did you act more positive than you felt?	Protective buffering
To what extent did you avoid talking about the issue?	
To what extent did you withhold potentially upsetting information from your partner?	
To what extent did you hide your worries?	
To what extent did you hide your anger?	
To what extent did you support your partner?	Supported partner
To what extent did you criticize your partner?	Criticized partner
To what extent did you understand your partner?	Understood partner
To what extent did you feel that your partner avoided talking about the issue?	Social constraints
To what extent did you feel that your partner supported you?	Perceived partner support
To what extent did you feel that your partner criticized you?	Perceived partner criticism
To what extent did you feel that your partner understood you?	Perceived partner understanding
**Mediators**	
How close do you feel to your partner right now?	Intimacy
How connected do you feel to your partner right now?	
How often did you have distressing thoughts about the cancer?	Intrusive thoughts
How often did you think about the cancer when you didn’t mean to?	
How often did you try to push away or avoid thoughts about the cancer?	Avoidance
How often did you avoid letting yourself get upset when you thought about the cancer or were reminded of it?	
**Outcomes**	
Dyadic Adjustment Scale item #31, posed only at the evening assessment • All things considered, what was your degree of happiness with your relationship today? (extremely unhappy, fairly unhappy, a little unhappy, happy, very happy, extremely happy, or perfectly happy; coded 0–6)	Relationship satisfaction
Profile of Mood States (Cranford et al., 2006)	Distress
• How vigorous do you feel right now?	
• How anxious do you feel right now?	
• How worn out do you feel right now?	
• How angry do you feel right now?	
• How sad do you feel right now?	
• How cheerful do you feel right now?	
• How fatigued do you feel right now?	
• How on edge do you feel right now?	
• How annoyed do you feel right now?	
• How discouraged do you feel right now?	
• How lively do you feel right now?	
• How uneasy do you feel right now?	
• How hopeless do you feel right now?	
• How resentful do you feel right now?	
• How exhausted do you feel right now?	
**Other/Ancillary**	
Please rate your current level of physical pain (no pain to pain as bad as you can imagine, 0–10 scale)	Pain
Please rate the overall quality of your sleep last night (not all restful to extremely restful, 0–4 scale; afternoon assessment only)	Sleep quality
To what extent has your physical health limited your usual activities today?	Physical health limitations

*All items posed on a 1–5 scale unless otherwise noted.*

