##### Ecological Momentary Assessment Data

The EMA dataset will be structured with study days (level 1 units) nested within couples (level 2 units). Each study day observation will have values for patient and partner reports of afternoon communication (holding back, disclosure, protective buffering, support, perceived partner holding back, perceived partner support) as exogenous predictors, afternoon reports of cognitive processing (avoidance, intrusive thoughts) or intimacy as mediators, and evening reports of psychological distress (POMS TMD composite) or relationship satisfaction as outcomes, all from the same day’s afternoon and evening assessments. In addition, autoregressive associations are included such that afternoon reports of mediators are predicted from the preceding evening’s reports of the same variables (e.g., patient evening report of intimacy on day t-1 predicts patient afternoon report of intimacy on day t) and each evening outcome variable is predicted by the immediately preceding observation on the same variable. See Figure 2 for an example treating intimacy as the mediator and distress as the criterion, with variables and paths of conceptual interest in black, and control variables and paths less central to the conceptual models in gray. Indirect associations of afternoon communication with change in same-day evening outcomes (distress or relationship satisfaction) *via* mediators assessed on that same afternoon will be estimated using a product-of-coefficients approach and evaluated using 95% confidence intervals.

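### The described EMA mediation model adjusts only for lagged mediators and outcomes, although daily sleep, pain and physical limitation are collected and could create or inflate an indirect association

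*Protocol article*

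**What the plan says.** Table 2 of the protocol article ends with an Other/Ancillary block of three items: "Please rate your current level of physical pain" (0–10), "Please rate the overall quality of your sleep last night" (0–4, afternoon prompt only) and "To what extent has your physical health limited your usual activities today" (1–5). No section gives these items an analytic use.

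The section Ecological Momentary Assessment Data describes the model in detail. "Each study day observation will have values for patient and partner reports of afternoon communication", namely "holding back, disclosure, protective buffering, support, perceived partner holding back, perceived partner support". The middle of the chain is "afternoon reports of cognitive processing (avoidance, intrusive thoughts) or intimacy as mediators". The end of the chain, taken from the later prompt of the same day, is "evening reports of psychological distress (POMS TMD composite) or relationship satisfaction as outcomes". Mediators are regressed on their own value from the evening before, and each outcome on its own preceding observation. Indirect associations are products of coefficients with 95% confidence intervals. The text refers to Figure 2 for control variables drawn in grey; the figure is not available here, and the only controls the text names are the lags.

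Sensitivity analyses with additional covariates are announced only for the fundamental-frequency models.

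**The concern.** Patients are receiving, or have received, systemic or hormone therapy. The Introduction names fatigue and pain as common in patients, and fatigue and sleep disturbance as common in partners. Such states vary from day to day. A bad day could plausibly make someone hold back more, have more intrusive thoughts or feel less close, and report more distress that evening. The distress composite contains physical content directly: items such as "How fatigued do you feel right now", and those on feeling vigorous, worn out, lively and exhausted, make 5 of 15.

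The planned controls do not close this path. Separating within-couple from between-couple variation removes stable differences in health, not new daily variation. Communication and mediator come from the same prompt, and the mediator is adjusted only for its value the evening before. Relationship satisfaction is asked only in the evening, so its lag is a full day old.

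The Discussion says that support for one or the other model would point interventions towards cognitive processing or towards intimacy. An indirect association produced by bad physical days would be read as such support.

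**Working it through.** The article gives no figure for the EMA model, so there is nothing of its own to reproduce. The check asks how large a spurious path an omitted daily state can produce.

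**Inputs from the article.** 14 EMA days; six communication predictors per person; mediator adjusted for its own lag. 264 dyads is the projected 12-month complete-case questionnaire sample, used here only as a convenient number of dyads.

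**Assumptions not in the article.** 25% of days missing; one daily physical state P with loading p on communication X, mediator M and outcome Y; variables close to unit variance; true X→M path zero; true M→Y path 0.1.

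**Dyad-days.** 264 × 14 = 3,696; 3,696 × 0.75 = 2,772.

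**One predictor, hand check.** With P omitted, X and M share covariance p × p, so the spurious X→M coefficient is about p². Its standard error is about 1/√2,772 = 0.019.

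| p | spurious path p² | z = p²/0.019 | chance that \|Z\| > 1.96 |
|---|---|---|---|
| 0.1 | 0.01 | 0.53 | 8% |
| 0.2 | 0.04 | 2.11 | 56% |
| 0.3 | 0.09 | 4.74 | 99.7% |

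The M→Y path of 0.1 has z of about 0.1/0.019 = 5.3, so it is nearly always significant and the X→M path decides the result. Simulation with the lags in the model gives 10%, 61% and 100%, in line with the hand check.

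**Six predictors entered jointly, hand check.** With a common inter-correlation r, each spurious coefficient falls to p²/(1 + 5r), and its standard error grows by √[(1 + 4r)/((1 − r)(1 + 5r))]. At r = 0.4 (assumed) the divisor is 3 and the factor is √(2.6/1.8) = 1.20, so the standard error is 0.0228.
- p = 0.1: 0.0033/0.0228 = 0.15, about 5%.
- p = 0.2: 0.0133/0.0228 = 0.58, about 9%.
- p = 0.3: 0.030/0.0228 = 1.31, about 26%.

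Simulation gives 6%, 11% and 23% per path. The chance that at least one of the paths is falsely positive is higher than the per-path figure.

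**Both true paths zero.** The product test is then very conservative. With one predictor, simulation gives almost nothing at 0.1, 17–31% at 0.2 and 91–99% at 0.3, for distress and for relationship satisfaction.

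**Inflation of a real effect.** With one predictor, a true indirect effect of 0.015 is estimated as about 0.024 at p = 0.2 and 0.036 at p = 0.3.

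**Effect of adjusting.** With P itself in both equations and a true M→Y path of 0.1, the false rate returns to about 5–6%. Imperfect measurement leaves a residue. In a setting with a true X→M path of 0.2 and no M→Y path, the rates at p = 0.3 are 83–96% unadjusted, 18–23% when P is measured with reliability 0.7, and about 7% with P itself. The spurious X→M path shrinks to about p²(1 − 0.7), for example 0.09 × 0.3 = 0.027 in place of 0.09.

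**The case against.** Five points on the other side deserve weight.

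- **A condensed article may leave covariates to the full plan, and nothing in the section is misstated.** This would settle the matter for an unspecified covariate list. Here the model is specified variable by variable, lags included, and the three collected items have no stated use. A reader might infer that the authors decided against adjusting for physical state. The article does not say so, and the ancillary label does not exclude the items as covariates.
- **Figure 2 may already contain them in grey.** This cannot be excluded. It limits the finding to the model as worded.
- **The magnitude is assumed.** This stands. All loadings are assumptions. The 264 dyads are not the EMA sample: EMA starts at baseline, when 434 dyads are planned, and usable days are unknown. A reader might take the one-predictor rates of about 60% and nearly 100% as the plan's error rates. The article lists six predictors per person and does not say clearly whether they enter together; joint entry cuts the per-path rates sharply.
- **Bad days affecting how much couples talk is not confounding in this model.** Correct. When no conversation took place, the communication items are not asked, so that route produces missing data. The response option of not feeling well, among the reasons for not talking, shows only that physical state is expected to bear on daily communication.
- **Noon pain and limitation are reported at the same prompt as communication and mediators and may be consequences of the conversation.** This stands, and it decides the form of the fix.

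**Conclusion.** The concern holds for the model as described: it omits measured daily physical states that can plausibly act on communication, mediator and outcome, and the named lag terms do not remove their day-to-day variation. Such an omission can create or inflate an indirect association. The article does not support saying that it will, or that any particular share of the EMA findings would be false.

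The size depends on within-day loadings that are not given. At 0.1 or below the problem is small under every setting tried. At 0.2 to 0.3 it runs from about 11–23% per path with six jointly entered correlated predictors to about 60–100% with one, against a nominal 5%. These figures rest on one physical factor with equal loadings, 2,772 dyad-days and a true mediator-to-outcome path of 0.1. More usable days would raise the rates.

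The plan calls its estimates indirect associations and the design is observational, so some residual confounding is unavoidable. The difference here is that relevant measures are already collected. Using them is worth doing before the analysis; it is not a fatal flaw in the plan.

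**What to change.** In the EMA analysis, add last night's sleep quality and the previous evening's pain and physical limitation as within-level covariates in the mediator and outcome equations of both dyad members, with the patient's values also in the partner's equations. These refer to a time before the noon communication window, so the conversation cannot have caused them.

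Report beside the model as described a sensitivity analysis that also adjusts for noon pain and limitation. The pre-conversation measures capture today's state only in part, while the noon items may over-adjust, so showing the results together lets the reader see how far the conclusion depends on the choice. State that error in single items leaves residual confounding. If the grey controls in Figure 2 already include these items, say so in the text.

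The cost is a few more within-level paths, a sentence or two in the plan and some days lost where the items are blank. The model already needs the previous evening's mediator, so using that evening's pain and limitation loses no further days unless those items themselves are missing. No new data are needed.

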### Laboratory-Based Couple Conversation

Couples are asked to participate in a 15-min cancer-related conversation that is video-recorded for later coding. Separate audio-recordings afford analysis of vocally encoded emotional arousal as described below. To assist participants in selecting topics of discussion for these conversations, we provide a list of cancer-related issues known to be relevant based on past research (Pistrang and Barker, 1992; Andrykowski et al., 1999). These topics are listed in Table 3. Both members of the dyad are instructed to independently review the list and select three topics that are meaningful to them, either because they have not yet discussed the issue but consider it important, or because it is something that remains unresolved or merits further elaboration. Space is included for participants to indicate unique topics of interest that are not on the list. After topics are chosen, couples review their six independently selected topics together and agree upon a single final topic for the conversation.

**TABLE 3 T3:** Possible discussion topics.

Your reaction to the diagnosis
Disruptions to your life caused by the cancer diagnosis and treatment
Managing cancer treatments
Managing treatment side effects
Dealing with medical staff
Having to give up or cut back from work or other important activities
Communicating with friends or family members about the cancer
Talking with children about the cancer
Maintaining a sex life
Being hospitalized
Plans for the future
Financial concerns
Getting support from friends and family
Completing household tasks
Completing daily activities
Dealing with changes in your/your partner’s physical appearance
Fears or worries about disease progression or death
Concerns about the quality of medical care
Concerns about your partner’s response to the illness

Couples are asked to sit in chairs placed approximately two feet apart and facing one another at a slight angle. They are instructed to speak to one another vs. the camera, and to allow the conversation to flow as it normally would outside of the research setting.

Prior to picking the topic and the conversation, couples engage in a modified DiapixUK task (Baker and Hazan, 2011) designed to elicit spontaneous speech of each partner for 1 min. These recordings are used to obtain an f_0_ baseline for analyses of vocally encoded emotional arousal. In this task, one dyad member is handed a picture and asked to describe what is depicted in it (for example, a beach scene) to their partner. After 1 min, the experimenter hands three pictures to the partner and asks them to select the one that was described. Roles are then reversed with a different set of pictures.

### Observational Coding

Two independent yet complementary coding systems are used to characterize participants’ communicative behaviors and affective expressions captured during the 15-min couple conversations: (1) the Asymmetric Behavior Coding System (Leo et al., 2020) and (2) the Relational Affective Topography System (Leo et al., 2020). Drawing from the Valence Affective Connection model (Leo et al., 2019), the systems delineate communicative behavior and affect as positive or negative and as promoting togetherness or engagement with the partner vs. individuation or separation from the partner.

Coding is being conducted in two waves with separate coding teams for the two systems, each consisting of 4–6 trained raters. For both systems, ratings are made independently by each coder and for each 3-min segment of the 15-min conversation. Separate passes are made for patients and partners. Order of viewing is randomized across coders, with approximately 30% of cases rated by all coding team members to assess inter-rater reliability. Coding teams meet weekly by videoconference to address problematic (highly discrepant) codes or cases.

The Asymmetric Behavior Coding System (ABCS) was adapted for this project to measure communicative behavior in the context of conversations regarding cancer. The ABCS consists of 24 behavior codes that load onto four higher-level factors as shown in the upper half of Table 4. Coders rate each behavior on a scale of 1 (no behavior present) to 7 (high levels of behavior present). Codes are not mutually exclusive. The frequency of particular behaviors, their intensity, and the context in which they occur are all used to determine the appropriate rating.

**TABLE 4 T4:** Key behaviors and affective expressions derived from the ABCS and RATS.

Asymmetric Behavior Coding System (ABCS)	
Positive approach/joining	Abbreviated coding descriptions/examples
• Maintaining/deepening	“Tell me more”
• Disclosure	“This is what I am thinking/feeling”
• Validation	“I hear you and I understand”
• Repair	“I’m sorry for what I just said/did a second ago”
• Collaboration	“Here’s what we can do to fix/solve x”
• Intimacy building	“I want to be closer/more connected to you”
• Justification	“Here’s what’s going on with me/why I did what I did”
• Requests	“Here’s what I want/need”
**Positive avoidance/individuating**	
• Accommodation	“Never mind, we don’t have to talk about it”
• Tough love	Holding partner accountable for actions without being judgmental
• Reassurance	“We’ve got this because we can handle it”
• Minimization	“We’ve got this because it’s not a big deal”
**Negative approach/joining**	
• Defensiveness	“It wasn’t my fault”
• Emotional protests	Whining
• Blame	“It’s your fault”
• Pressures for change	“You need to do this”
• Domineering	“This is what you think/feel”
• Belligerence	Taunting
• Contempt	“I don’t value you”
**Negative avoidance/individuating**	
• Controlling the conversation	“I’m talking right now”
• Withdrawal	“I don’t want to be here”
• Avoidance	“I don’t want to talk about this”
• Stonewalling	The kind of things you do on a plane/train/bus when you don’t want to talk to someone
• Submit	“Fine, whatever you say as long as we can be done talking about it”
**RELATIONAL AFFECTIVE TOPOGRAPHY SYSTEM (RATS)**	
Flat emotion	
• Boredom	
• Indifference	
Positive joining emotion	
• Warmth	
• Appreciation	
• Kindness	
Positive individuating emotion	
• Happiness	
• Enthusiasm	
• Amusement	
• Satisfaction	
Hard negative emotion	
• Anger	
• Disgust	
• Frustration	
• Outrage	
Soft negative emotion	
• Sadness	
• Fearfulness	
• Loneliness	
• Guilt	
• Vulnerability	

While the ABCS focuses on the content and function of specific communicative behaviors, the Relational Affective Topography System (RATS) focuses on the affective quality of expressions. The RATS involves three steps. First, coders record whether positive emotions, negative emotions, and flat emotions as defined in the lower half of Table 4 are observed in a given 3-min segment (yes or no for each). Second, coders classify any positive emotions observed as positive joining (making emotional room for the other partner) or positive individuating (taking emotional space in the conversation), and any negative emotions observed as hard (conveying a sense of injustice or ineffectiveness) or soft (conveying unguardedness and inviting a protective response). Note that for both of these distinctions, the two options are not mutually exclusive for a segment, i.e., both can be observed within a given segment. Third, if flat emotions (characterized by low activation and arousal) were observed in step 1, the extent to which specific constituent emotions, boredom and indifference, were observed are rated on a 0–7 (none to high levels of the emotion) scale. If positive joining emotions were observed in step 1, the extent to which warmth, appreciation, and kindness were observed are rated on the same 0–7 scale, and so on for positive individuating, negative emotion, and soft negative emotion. Please see the lower half of Table 4 for a list of these specific constituent emotions.

